## Introduction

### Background and rationale {6a}

Pain is often considered an inevitable outcome of surgery. Postcraniotomy patients have frequently been assumed to experience modest pain among all surgeries. However, current evidence suggests that pain after neurosurgical procedures is more severe than expected [1, 2]. A prospective study of 187 patients demonstrated that pain was common in the first 2 days after major craniotomy, with approximately 70% of patients reporting moderate to severe pain during the 1st postoperative day and 48% of patients complaining of pain scores greater than or equal to 4 on the 2nd postoperative day [2]. Sympathetically mediated hypertension caused by inadequate analgesia may lead to an increased risk of postoperative complications, such as arterial hypertension, intracranial hemorrhage, prolonged hospital stays, and mortality [3]. In addition, undertreated acute postoperative pain may predict the development of chronic pain [4–6]. Therefore, optimal pain management is of great importance for improving postoperative recovery and patient comfort [7].

Opioids are commonly used for postoperative analgesia, but the use of opioids for neurosurgical procedures is limited by potential side effects such as sedation, miosis, nausea, vomiting, and respiratory depression [8]. Multimodal analgesic techniques, such as combining an opioid with supplemental analgesics (including nonsteroidal anti-inflammatory drugs (NSAIDs), scalp infiltration, and scalp nerve blocks), typically result in improved analgesia with concurrent reductions in the incidence of systemic opioid-related adverse effects [8, 9]. The neural tissue of the brain does not contain any pain receptors. Most pain following craniotomy arises from the pericranial muscles and soft tissues of the scalp [10]. Therefore, scalp nerve blocks, which suspend the function of the sensory nerve fibers in the superficial and deep soft tissue layers, can reduce the consumption of analgesic drugs and may enhance early postoperative recovery.

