### Eligibility criteria {10}

#### Inclusion criteria

Patients scheduled for elective supratentorial craniotomy under general anesthesia will be consecutively screened for eligibility based on the following criteria: age 18 to 64 years; an American Society of Anesthesiologists (ASA) physical status of I, II or III; and a preoperative Glasgow Coma Scale (GCS) score of 15/15. Each participant must be able to understand the nature and potential individual consequences of the clinical trial.

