#### Secondary outcomes

The cumulative amount of sufentanil consumption by PCA at 4, 12, 24, and 48 h postoperatively and the number of participants who have no PCA press will also be documented.The NRS (11-point scale in which 0 = no pain to 10 = worst imaginable pain) will be determined at fixed intervals after the procedure, i.e., 2, 4, 8, 12, 16, 20, 24, and 48 h. An NRS score ≥4 will be considered significant or moderate pain. An NRS score ≥7 will be considered severe pain. Meanwhile, the localization of the site of the pain will also be documented.The GCS [40] will be assessed at predetermined intervals after the procedure, i.e., 2, 4, 8, 12, 16, 20, 24, and 48 h.Postoperative observation: postoperative nausea and vomiting (PONV), bradycardia, hypotension, and emergence delirium within 48 h after surgery will be recorded. Vomiting will be defined as the forceful expulsion of gastric contents, and nausea will be defined as an unpleasant sensation associated with the urge to vomit. Bradycardia will be defined as HR< 60 beats/min in at least two instances more than 5 min apart. Hypotension will be defined as any of the following: systolic BP < 90 mm Hg for 5 min or a 35% decrease in mean arterial blood pressure [41]. Emergence delirium will be assessed by the Sedation Agitation Scale (SAS), a 7-point scale on which a higher score represents greater agitation [42]. The time in the PACU and the length of stay (LOS) will be recorded. The LOS will be defined as the number of nights spent in the hospital after surgery. The postoperative data will be collected by reviewing each patient’s medical record.Postoperative satisfaction: Patient satisfaction will be assessed by the patient satisfaction score (PSS) (0 for unsatisfactory to 10 for very satisfactory) at 2, 4, 8, 12, 16, 20, 24, and 48 h after surgery.

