## Statistical methods

### Statistical methods for primary and secondary outcomes {20a}

Normality and homogeneity of the data distribution will be evaluated using the Shapiro Wilkinson test. Baseline characteristics, when they consist of descriptive variables with a normal distribution, will be described using the mean ± SD. Data with a skewed distribution will be presented as the median with the 25th and 75th percentiles. Dichotomous and categorical data will be described as frequencies and percentages. Group comparisons will be performed by using Student’s *t* test or the nonparametric Wilcoxon-Mann-Whitney test for quantitative variables and Pearson’s chi-squared test or Fisher’s exact test for categorical variables. NRS score and GCS at different time points will be analyzed with repeated measures analysis of variance (ANOVA) using time as the between-subjects factor. Details of statistical analysis will be fixed, at the latest, in the statistical analysis plan that will be prepared before the database is locked and analysis is commenced. The statistical tests will be 2-tailed and *P* < 0.05 will be considered statistically significant. SPSS software (version 25) will be used to conduct all analyses.

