### Adverse event reporting and harms {22}

An AE will be defined as any untoward medical occurrence such as local hematoma, nerve injury, intra-arterial injection, allergic or toxic reaction, or facial nerve paralysis from scalp nerve blocks. Patients with blurry vision and tinnitus will be carefully observed postoperatively. Meanwhile, any signs of glucocorticoid-associated systemic toxicity such as infection will also be addressed according to the current practices and will be recorded. SAEs will include death, immediate life-threatening conditions, coma, inpatient hospitalization, or prolongation of the existing hospitalization. Serious adverse events (SAEs) occurring in the REDUCE trial must be signed and submitted to the trial management committee within 24 h after they are recognized. All SAEs that occur (including SAEs in withdrawn participants) must be continuously monitored until there are no signs or symptoms or until the participants are in stable condition. Anonymized data on all AEs must be annually reported to the IRB.

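### Mean GCS by repeated measures ANOVA is the only GCS analysis named, though all patients start at the maximum of 15; it cannot show how many deteriorated

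*Protocol article*

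**What the plan says.** - **Entry.** The inclusion criteria require "a preoperative Glasgow Coma Scale (GCS) score of 15/15", the maximum of the scale.
- **Measurement.** GCS is listed under Secondary outcomes and "will be assessed at predetermined intervals after the procedure, i.e., 2, 4, 8, 12, 16, 20, 24, and 48 h". That is eight readings per patient. No fall is defined as an event and no threshold is given.
- **Analysis.** Under Statistical methods {20a}, "NRS score and GCS at different time points will be analyzed with repeated measures analysis of variance (ANOVA", with the specification "using time as the between-subjects factor". GCS and the pain score share this one sentence, and no other method is tied to GCS.
- **Other tools in the same section.** It plans a normality check, medians for skewed data, the t test or Wilcoxon-Mann-Whitney test for quantitative variables, and "Pearson’s chi-squared test or Fisher’s exact test for categorical variables". It adds that "Details of statistical analysis will be fixed, at the latest, in the statistical analysis plan".
- **Other records of neurological harm.** Under Adverse event reporting {22}, "SAEs will include death, immediate life-threatening conditions, coma, inpatient hospitalization, or prolongation of the existing hospitalization". Emergence delirium is scored on the Sedation Agitation Scale, and Table 1 schedules it at the same visits as GCS.

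**The concern.** A 0 to 10 pain score spreads over its range, so a mean over time is a reasonable summary. GCS in this trial does not behave that way. It is ordinal, bounded above, and starts at its bound in every patient. Normality and equal variance fail by design, and the useful information lies in the few patients whose score falls: how many there are, how far they fall and for how long. A mean merges these three into one small number.

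The stake is interpretation. The Background names serious consequences of poor analgesia, "such as arterial hypertension, intracranial hemorrhage, prolonged hospital stays, and mortality", and sedation as an opioid side effect. The Discussion looks ahead to calling the adjuvant effective and free of side effects. Two mean GCS curves that lie almost on top of each other would be easy to cite in support, even if more patients in one arm had deteriorated.

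This is a stated choice of method, not a detail left open. It is also separate from the faulty factor specification in the same sentence (time is a within-subject factor, and treatment group is not named). A correctly specified group-by-time ANOVA would still report GCS on the mean scale.

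**Working it through.** The protocol gives no GCS standard deviation, deterioration rate or power, so there is no figure of its own to reproduce on this point.

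**Inputs from the protocol.** Entry GCS 15; 8 visits; 78 patients per arm; two-sided 5% level.

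**Assumptions.** 12% versus 1% of patients deteriorate. Depth and duration of falls vary. The background chance of a reading of 14 varies, from 25% at 2 h declining to 2% at 48 h, down to none.

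**Step 1: what the mean shows.** With a fall of d points lasting v visits, and ignoring overlap with background readings,

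mean difference = (p1 − p0) × d × v / 8, with p1 − p0 = 0.12 − 0.01 = 0.11.

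- 2 points, one visit: 0.11 × 2 × 1 / 8 = 0.028
- 3 points, one visit: 0.11 × 3 × 1 / 8 = 0.041
- 2 points, two visits: 0.11 × 2 × 2 / 8 = 0.055
- 4 points, four visits: 0.11 × 4 × 4 / 8 = 0.22

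The excess of patients is 11 percentage points in all four cases, while the mean difference varies eightfold. Conversely, 0.055 also arises from a 44-point excess of patients who read 14 once (0.44 × 1 × 1 / 8). The mean cannot separate many trivial dips from a few real falls.

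**Step 2: a worked example.** Let 8 of 78 versus 1 of 78 patients have a 4-point fall at one visit.

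- If all the falls occur at the same visit, the mean difference there is 7 × 4 / 78 = 0.36. Averaged over eight visits it is 0.36 / 8 = 0.045.
- Risk difference: 10.3% − 1.3% = 9.0 percentage points.
- Fisher's exact test: p = 0.034.
- t test on patient means (equivalent to the ANOVA group effect), all other readings 15: p = 0.016.

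The estimate is uninformative, yet the test still finds the difference.

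**Step 3: power at 12% versus 1%.** Simulated with 78 per arm and 8 visits. Fisher's test is on any GCS of 13 or less. The rows come from separate runs of 600 to 1,500 trials, so differences of a few hundredths mean nothing.

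| Background of GCS 14 | Fall | ANOVA group effect | Fisher |
|---|---|---|---|
| 25% to 2% | 2 points, 1 visit | 0.27 | 0.78 |
| 25% to 2% | 3 points, 1 visit | 0.44 | 0.77 |
| 25% to 2% | 2 points, 2 visits | 0.52 | 0.76 |
| 25% to 2% | 4 points, 2 visits | 0.74 | 0.77 |
| 25% to 2% | 4 points, 4 visits | 0.86 | 0.76 |
| 10% to 1% | 2 points, 1 visit | 0.40 | 0.71 |
| 5% to 0.5% | 2 points, 1 visit | 0.55 | 0.77 |
| 2% to 0% | 2 points, 1 visit | 0.68 | 0.73 |
| none | 2 points, 1 visit | 0.85 | 0.75 |

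The first row is the least stable; repeated runs put the ANOVA between about 0.2 and 0.3.

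**Step 4: other rates.** Falls of 2 to 7 points at one visit, two visits or sustained; background 25% to 2%.

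| Rates | ANOVA group effect | Fisher |
|---|---|---|
| 2% vs 10% | 0.36–0.45 | 0.40–0.42 |
| 3% vs 15% | 0.61–0.66 | 0.68–0.71 |
| 5% vs 15% | 0.38–0.47 | 0.46–0.47 |
| 5% vs 20% | 0.67–0.72 | 0.77–0.79 |

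Mean differences were 0.04 to 0.15 points for one- or two-visit falls and 0.21 to 0.37 for sustained ones. The group-by-time test had power of 0.02 to 0.04 for one- or two-visit falls and 0.36 to 0.62 for sustained ones.

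**The case against.** The strongest reply has four parts.

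1. **GCS is not where this trial looks for harm.** A reader might infer that GCS is the trial's neurological safety measure, or its only scheduled one. The protocol says neither. GCS is one of several secondary outcomes. Coma, life-threatening conditions and death are serious adverse events, adverse events are recorded at every visit to discharge, a data monitoring committee reviews safety, and the Sedation Agitation Scale is scored too. This stands. What remains is narrower: the serious-event definition names coma but no lesser fall in GCS, and lesser falls are what the mean obscures.

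2. **The signal is not averaged away.** A reader might infer that ANOVA would miss an excess of deterioration. As a general claim this fails. The large power gap needs brief, shallow falls and frequent early readings of 14. Elsewhere the group effect is close to Fisher's test or better. The objection does not rescue the estimate, which stays a small fraction of a point throughout.

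3. **The analysis plan may add counts.** It may, so one cannot say that deteriorating patients will never be compared. But the protocol has already attached a method to GCS, and that method is the point.

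4. **A cut-off is a preference.** Partly true. No threshold comes from the documents, and an ordinal or rank-based analysis would also meet the scale objection. A count is suggested because it yields a risk difference that clinicians can read directly.

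**Conclusion.** The point holds as one about the scale of the summary, and it is worth changing. The named method reports a ceilinged ordinal score as a mean. With 12% versus 1% of patients deteriorating, an 11-point risk difference would appear as about 0.03 to 0.2 GCS points. That conclusion rests on the entry criterion and simple arithmetic; only its size depends on the assumed rates.

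The power argument is conditional and should not carry the case. It runs from about 0.27 against 0.78 in the least favourable setting to equal or better than Fisher's test with no background or with larger or sustained falls. None of the rates, depths or backgrounds comes from the protocol. The documents do not support a claim that the trial would be blind to neurological harm.

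**What to change.** In Statistical methods {20a}, take GCS out of the ANOVA sentence and make its main comparison the number of patients per arm with a prespecified fall from 15 at any scheduled visit to 48 h. The sponsor should set the threshold before unblinding, as an analysis definition and not a management rule; at least 2 points is one example. Report the risk difference with 95% CI and Fisher's exact test, which the section already names. Tabulate each patient's lowest GCS by arm. Mean GCS over time may stay as description, and the pain score can keep a repeated measures analysis once its factors are correctly stated.

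The cost is wording in the protocol or analysis plan; all eight readings and the entry value are already collected. The downside is that a cut-off discards some ordinal information, such as 14 versus 15, which the table of lowest scores covers.

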### Trial design {8}

This study is a prospective, single-center, parallel-group randomized controlled, superiority trial. The planned study has been registered at ClinicalTrials.gov under the identifier NCT04648358. See Fig. 1 for the flow chart. Additional File 1 shows the Standard Protocol Items: Recommendations for Interventional Trials (SPIRIT) checklist for study protocols.

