### Interventions description {11a}

#### Intervention and control groups

After the initiation of the study, eligible participants will be consecutively screened for trial inclusion. A total of 156 participants will be randomly assigned to one of the two groups using a computer-generated list.

The control group will receive scalp nerve blocks with 0.5% bupivacaine 21 ml with epinephrine at 1:200,000, plus normal saline 1 ml.

The DEX_4mg_ group will receive scalp nerve blocks with 0.5% bupivacaine 21 ml with epinephrine at 1:200,000, plus 4 mg dexamethasone (1 ml).

An independent researcher will prepare the study solution in a separate operating room. After opening the envelope containing the treatment allocation, the study solutions will be prepared in 50-ml syringes for scalp nerve blocks with 23-gauge needles and will be numbered by an independent researcher. After induction, the assigned solutions will be used for nerve blocks injections by the anesthesiologist, who will be blinded to the group allocations.

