## Assignment of interventions: allocation

### Sequence generation {16a}

SPSS software version 25 will be used to carry out sample randomization with a 1:1 ratio to one of the two groups by a statistical assistant, who will not be involved in patient assessments.

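### The repeated measures ANOVA of NRS and GCS gives time the between-subjects role that belongs to randomised group, and names neither group nor group × time

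*Protocol article*

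**What the plan says.** The protocol article, Statistical methods for primary and secondary outcomes {20a}, gives NRS and GCS a sentence of their own: the scores at the different time points will be "analyzed with repeated measures analysis of variance (ANOVA) using time as the between-subjects factor". Time is the only factor named.

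Under Secondary outcomes, NRS "will be determined at fixed intervals after the procedure, i.e., 2, 4, 8, 12, 16, 20, 24, and 48 h", and GCS "will be assessed at predetermined intervals after the procedure, i.e., 2, 4, 8, 12, 16, 20, 24, and 48 h". Table 1 marks both scores at the same eight postoperative times.

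Trial design {8} describes a "prospective, single-center, parallel-group randomized controlled, superiority trial". The interventions section adds: "A total of 156 participants will be randomly assigned to one of the two groups". Section {20a} also sets the test level: "The statistical tests will be 2-tailed and *P* < 0.05 will be considered statistically significant". It leaves details to a statistical analysis plan, to be fixed before the database is locked.

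**The concern.** A between-subjects factor takes one value per patient; a within-subject factor changes inside the patient. Here every patient contributes a score at each of the eight times and belongs to one randomised group, so the label has been put on the wrong factor. The factor that carries the trial's question is not in the sentence.

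What is at stake is the analysis of pain over time. Relief of postcraniotomy pain is the stated objective, and NRS is its direct measure among the secondary outcomes. An analyst who follows the sentence tests whether scores change over time, not whether they differ between arms. An analyst who repairs it halfway, by adding group but leaving the eight scores as if they came from different patients, gets a test of treatment with a far too small error term.

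**Working it through.** The plan states no figure for this analysis, so there is none to reproduce. The check compares the factor roles with the design and then sizes the two ways in which the sentence could be followed.

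**Inputs**

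- Patients: N = 156 in two groups, 1:1, so 78 per group (Interventions description; Sequence generation {16a}).
- Times: T = 8 (Secondary outcomes; Table 1).
- Test level: two-sided 0.05 (section {20a}).
- Within-patient correlation ρ: not given in the documents. Assumed equal between all pairs of times, with range 0 to 0.7.

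**Step 1. Factor roles**

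| Factor | Varies | Role by design | Role in {20a} |
|---|---|---|---|
| Time | within each patient, 8 values | within-subject | between-subjects |
| Randomised group | between patients, 2 values | between-subjects | not named |
| Group × time | tested within patients | interaction | not named |

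**Step 2. Degrees of freedom with the roles put right**

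- Observations: 156 × 8 = 1248.
- Group: F(1, 156 − 2) = F(1, 154).
- Time and group × time: F(7, 154 × 7) = F(7, 1078).

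**Step 3. Literal reading: time is the only factor and scores are independent**

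There is no group term, so there is no treatment test. For time, the error df is 1248 − 8 = 1240. With no true change over time, the time mean square has expectation σ²(1 − ρ), while the error mean square stays near σ². The F ratio therefore shrinks by 1 − ρ, and type I error ≈ P(F(7, 1240) > 2.017/(1 − ρ)).

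| Assumed ρ | 2.017/(1 − ρ) | Formula | Simulated |
|---|---|---|---|
| 0 | 2.02 | 0.050 | 0.049 |
| 0.3 | 2.88 | 0.005 | 0.004 |
| 0.5 | 4.03 | 0.0002 | 0.000 |
| 0.7 | 6.72 | < 0.0001 | 0.000 |

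**Step 4. Half-repaired reading: group added, all 1248 scores still independent**

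The error df becomes 1248 − 16 = 1232, where 154 is right. The variance of a group mean is understated by 1 + (T − 1)ρ = 1 + 7ρ, so type I error for group ≈ 2 × [1 − Φ(1.96/√(1 + 7ρ))].

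| Assumed ρ | 1 + 7ρ | 1.96/√(1 + 7ρ) | Formula | Simulated |
|---|---|---|---|---|
| 0 | 1.0 | 1.960 | 0.05 | 0.05 |
| 0.3 | 3.1 | 1.113 | 0.27 | 0.26 |
| 0.5 | 4.5 | 0.924 | 0.36 | 0.34 |
| 0.7 | 5.9 | 0.807 | 0.42 | 0.42 |

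**Step 5. Correct structure**

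In the same simulations, type I error is 0.046 to 0.049 for group tested against between-patient variation, and 0.047 to 0.059 for time as a within-subject factor, over ρ from 0 to 0.7.

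All simulations used 78 per group, 8 times, normal compound-symmetric data with no true effect, and 4,000 replicates.

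**The case against.** The strongest defence is that this is a slip of the pen. Repeated measures ANOVA and time as a between-subjects factor contradict each other, and in a parallel-group trial the obvious reading is that group was meant. That is plausible, and it lowers the weight of the point. It does not remove it: nothing elsewhere in the article corrects the label.

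A second defence is that details are left to the statistical analysis plan. That covers what is left open. Here the factor's role has been stated, and stated wrongly; a plan that follows it inherits the error, and one that departs from it creates a discrepancy.

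A third defence is that the preceding sentence in {20a} provides a t test or Wilcoxon-Mann-Whitney test for quantitative variables, which could compare the groups on NRS or GCS at single times. This stands in part. A reader might infer that the protocol has no means at all of comparing pain scores between arms, and that would go too far. But the repeated scores are assigned specifically to the ANOVA, and it is that analysis which lacks a treatment term.

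A reader might also infer that the plan as written will produce false positive pain and GCS differences at rates of about 27% to 42%. The documents do not support this. Those rates belong to a model that adds a factor the sentence omits and drops the repeated structure it names.

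**Conclusion.** The sentence is wrong as written and should be fixed. Time is given the role of randomised group, and neither group nor group × time appears. Followed literally, the analysis yields no treatment comparison and an invalid, over-conservative test of time. The inflated error for group arises only under the half-repaired model. Every type I error figure at non-zero correlation rests on a correlation assumed here, with equal correlation and normal data.

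The weight is moderate. Only secondary outcomes are touched; the primary outcome (time to first PCA press) and the sample size are not affected.

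A reader might go further on GCS and conclude that it will pile up at its maximum, so that ANOVA is unsuitable. Entry requires "a preoperative Glasgow Coma Scale (GCS) score of 15/15", so a ceiling is a reasonable inference. The article gives no postoperative GCS distribution, however, and this should be treated as a contingency, not as a demonstrated fault.

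**What to change.** Replace the sentence in section {20a}, and carry it into the statistical analysis plan before database lock, with:

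> NRS and GCS will be analysed with a repeated measures model with treatment group as the between-subjects factor, time as the within-subject factor and the group × time interaction. The treatment test will be the group effect together with group contrasts at each time.

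A mixed model for repeated measures is an acceptable equivalent but is not needed to cure the error. For GCS, add that an ordinal or binary repeated analysis will be used if scores cluster at 15.

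The cost is one sentence of wording. Data collection, sample size and the primary analysis do not change.
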